#### Waiting-list control group

2.7.3

The participants in the waiting group will not be treated within 10 days during the study period, and then treated same as the positive control group from the 11th day.

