##### rTMS at r-DLPFC

2.7.2.1

Low-frequency (1 Hz) rTMS at r-DLPFC is recommended for sleep disorders in the *Chinese experts consensus on rTMS* (level of evidence: level II/III)^[12]^ and *Guidelines for The Diagnosis and Treatment of Insomnia in China*.^[25]^ After preparation, test RMT: the measurement is same as the experimental group; locate the stimulus area: the stimulation coil will be placed tangent to the scalp on the r-DLPFC (8 cm in front of the midpoint of the connection between 2 ear tips, and then 6 cm toward the right side); set the stimulus parameters: the intensity is selected 100% RMT. Other parameters are same as the experimental group. Participants will be treated 2 sessions per day for 10 consecutive days.

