### Adverse events observation

2.8

It could be that patients with epilepsy or headache, scalp discomfort, and tinnitus at stimulating are more likely related to rTMS. Regional skin numbness around the HT7 acupoint occur in patients is probably connected to rMS at HT7 acupoint. With the patients’ diary, all adverse events are to be recorded and measured during treatment and the follow-up period. Serious adverse events should be reported to the principal investigator immediately. All details will be documented, coil location and stimulus intensity adjustment (avoid the more sensitive orbitofrontal cortex, 100% RMT → 80% RMT), as well as appropriate medical care will be given at once. For the participants with severe CI during study, they would be administered with Eszopiclone tablets (3 mg Qn). However, if the subjects cannot tolerate the 80% RMT intensity and/or take Eszopiclone tablets more than twice a week, they will be considered as drop outs.

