### Primary outcomes

2.9

The ISI scores for the severity of CI before and the 10th day of treatment, 30th day of follow-up. The RMT for excitability of the motor cortex before and the 10th day of treatment, 30th day of follow-up.

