### Randomization

2.12

After recruitment, the patients who meet the eligibility criteria would be randomly and equally divided into 3 groups at a ratio of 1:1:1 with random number table method. Each subject will be registered with a unique ID. After the clinical screening and getting the informed consent forms, subjects will be assigned to experimental group (rTMS at HT7), positive-control group (rTMS at r-DLPFC), and waiting-list control group (no treatment) randomly. Each subject will receive the different stimulation forms, even no stimulating, whereas all subjects will be aware of the grouping.

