#### Primary outcomes

2.13.1

We will use univariate repetitive measurement deviation analysis with ISI scores and RMT before and the 10th day of treatment, 30th day of follow-up as the outcomes. A significant effect of group indicates that the ISI scores and RMT are different between groups after intervention.

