#### Safety evaluation

2.13.3

Adverse events recorded in the patients’ diary will be analyzed as a multiply variable. The number and percentage of patients with AE will be calculated and compared using Chi-squared test.

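### The waiting-list arm gets r-DLPFC rTMS from day 11 but is analysed as a control through day 30, which leaves no untreated comparison at that visit and dilutes the planned group effect

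*Protocol article*

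**What the plan says.** All references are to the protocol article.

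- **Treatment of the arm.** Under section 2.7.3 the waiting list "will not be treated within 10 days during the study period, and then treated same as the positive control group from the 11th day". The positive-control course that it copies is set in section 2.7.2.1: "Participants will be treated 2 sessions per day for 10 consecutive days".
- **Primary outcomes.** Section 2.9 sets the same three visits for both: "The ISI scores for the severity of CI before and the 10th day of treatment, 30th day of follow-up" and "The RMT for excitability of the motor cortex before and the 10th day of treatment, 30th day of follow-up".
- **Primary analysis.** Section 2.13.1: "We will use univariate repetitive measurement deviation analysis with ISI scores and RMT before and the 10th day of treatment, 30th day of follow-up". It then reads a significant group effect as showing that the groups differ after intervention. It sets no restriction for the waiting list at day 30.
- **Label of the arm.** The abstract and section 2.12 call the waiting list a no-treatment group. The abstract has all arms move to a 20-day follow-up after day 10 and does not mention the delayed treatment.
- **Secondary scales.** Sections 2.10 and 2.13.2 use baseline and day 10 only. The abstract lists day 30 for them as well.
- **Adverse events.** Section 2.8: "all adverse events are to be recorded and measured during treatment and the follow-up period". Section 2.13.3: "The number and percentage of patients with AE will be calculated and compared using Chi-squared test". Neither sets a time window for the waiting list.

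**The concern.** A waiting-list arm serves as an untreated comparator only while it is untreated. Here that is days 1 to 10. By day 30 the arm has been given the positive-control treatment, so a comparison with it is immediate treatment against delayed treatment. The stated primary analysis does not separate the two periods. It pools a visit with an untreated control and a visit with a treated one into a single group effect, and interprets only that effect.

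Two things are at stake. First, a day-30 difference from the waiting list, or the lack of one, could be taken as evidence about the effect against no treatment, which it cannot be. Second, the group effect loses part of the active-versus-waiting separation that exists at day 10. If active effects wane by day 30, the more recently treated waiting list could even look better than the active arms at that visit.

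The adverse-event comparison has a similar gap. With no window, stimulation-related events from day 11 could be counted in the arm labelled as untreated.

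**Working it through.** The article gives no effect size, SD, correlation or power for its 45 participants, so there is no stated figure to reproduce beyond 45/3 = 15 per arm.

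**Timeline.** The waiting list is untreated on days 1 to 10. A 10-day course starting on day 11 runs to day 20. This is inferred from sections 2.7.3 and 2.7.2.1, since no end date is stated. Day 30 is then about 10 days after the last session for the waiting list (30 − 20) and 20 days for the other two arms (30 − 10).

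**Expected contrast.** Assume that both active arms differ from untreated by d at day 10 and keep that difference at day 30, and that the waiting list reaches a fraction k of d by day 30. The active-minus-waiting contrast is 0 at baseline, d at day 10 and (1 − k)d at day 30. The mean over three visits is (2 − k)d/3:

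- k = 0 (no crossover): 2d/3
- k = 0.5: d/2
- k = 1 (full catch-up): d/3

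Full catch-up therefore halves the contrast.

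**Power of the three-arm group effect.** Assumptions: d = 1 SD, equal active arms, n = 15 per arm, alpha 0.05, F with 2 and 42 degrees of freedom.

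- The variance of a three-visit mean is (1 + 2ρ)/3, which is 0.667 at ρ = 0.5.
- With two equal arms and one that differs by c, the sum of squared deviations of the arm means is (2/3)c².
- The noncentrality is n(2/3)c² divided by that variance.

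At ρ = 0.5:

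- k = 0: 15 × (2/3) × (2/3)² / 0.667 = 6.67, power 0.60
- k = 0.5: 15 × (2/3) × (1/2)² / 0.667 = 3.75, power 0.37
- k = 1: 15 × (2/3) × (1/3)² / 0.667 = 1.67, power 0.18

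Over the correlation range:

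| ρ | No crossover | Half catch-up | Full catch-up |
|---|---|---|---|
| 0.3 | 0.70 | 0.45 | 0.22 |
| 0.5 | 0.60 | 0.37 | 0.18 |
| 0.7 | 0.52 | 0.31 | 0.16 |

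Section 2.1 gives 54 participants instead of 45. With 54/3 = 18 per arm and ρ = 0.5, the fall is from 0.69 to 0.22, so the pattern does not depend on which total is right.

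**Day 10 alone.** The contrast is the full d. The noncentrality is 15 × (2/3) × 1² / 1 = 10, and power of the three-arm test is 0.79.

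**What is unaffected.** At day 10 the waiting list has had no study stimulation, so that contrast is clean. HT7 versus r-DLPFC does not involve the waiting list, so the crossover does not bias it at either visit.

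**The case against.** The strongest reply has four parts.

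**Group-by-time.** The same repeated-measures model yields a group-by-time test, and its power is not damaged by full catch-up. The waiting-list contrast has profile (0, d, 0) with crossover and (0, d, d) without. The squared deviations around the profile mean sum to 2d²/3 in both cases. Under the same assumptions and sphericity, power is 0.66, 0.82 and 0.97 at correlations 0.3, 0.5 and 0.7. Section 2.13 also mentions ANOVA or Kruskal–Wallis by measurement time. This stands in part: the data would not hide the day-10 separation. But section 2.13.1 interprets only the group effect, and no model term turns day 30 into an untreated comparison.

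**Assumed inputs.** The power figures rest on an effect size, persistence and a degree of catch-up that the article does not give. This stands, and they are illustrations only.

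**Pilot and noninferiority design.** The named question is HT7 against r-DLPFC, in a self-described pilot, and the article makes no explicit day-30 claim against no treatment. This stands and limits the reach of the point. It does not repair the analysis as stated.

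**Adverse events.** Section 2.13.3 gives no grouping rule, and such rules often sit in a fuller document. This stands, so that part is a clarification.

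A reader might go further and infer that the crossover removes most of the waiting-list signal, or reverses the meaning of the test. Neither follows. Full catch-up removes half of the three-visit contrast; the drop from d to 2d/3 comes from averaging in baseline. It is true that, under the same assumptions at correlation 0.5, the group effect has power 0.47 if HT7 is inert against 0.18 if it equals r-DLPFC. But a three-arm omnibus test is not a test of HT7 efficacy. In the inert case it correctly detects that the arms differ.

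**Conclusion.** The point holds. As written, the primary analysis of ISI and RMT treats the waiting list as one control throughout, although it is a delayed r-DLPFC arm by day 30. That the arm stays in at day 30 is read from the unrestricted wording of sections 2.9 and 2.13.1; no sentence limits it to day 10.

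That day 30 has no untreated comparison follows from the text and needs no assumption. The size of the dilution does need assumptions: up to half of the three-visit contrast for catch-up between none and full, with effects that persist to day 30.

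The damage is confined to the omnibus group effect and to day-30 contrasts with the waiting list. A reader might infer that the secondary scales are also affected. The body does not support this, because sections 2.10 and 2.13.2 already stop at day 10. Nor does any sentence assign events after day 10 to no treatment; the article leaves that open.

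**What to change.** - In section 2.13.1, restrict ISI and RMT comparisons with the waiting list to day 10. At day 30 compare only HT7 with r-DLPFC. Report waiting-list day-30 data separately and descriptively, as delayed r-DLPFC treatment.
- In section 2.13.3, limit the waiting-list adverse-event comparison to days 1 to 10, or tabulate events by the treatment received at onset.
- Reconcile the abstract and section 2.12 with section 2.7.3 on what this arm receives after day 10.
- Leave the secondary-scale analysis in the body unchanged, and reconcile the abstract's day-30 mention of those scales with it.

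The cost is wording in the analysis plan and tables, settled before the data are analysed. Treatment, visits and numbers do not change. The waiting list's day-30 data no longer contribute to a controlled comparison, but they could not have supported one against no treatment.

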**Methods/design::**

This is a 3-armed randomized positive-controlled noninferiority clinical trial. We will allocate 45 subjects aged between 18 and 65 years old, diagnosed with initial chronic insomnia over 3 months to 3 groups randomly in a ratio of 1:1:1. Patients in the experimental group will be treated with rMS at HT7 acupoint while the others in the control group will be treated with rTMS at r-DLPFC or waiting treatment. All will be given rMS at HT7 or rTMS at r-DLPFC or no treatment for 10 days, and then received 20-day follow-up. Patients will be evaluated with the insomnia severity index and Pittsburgh sleep quality index for sleep state, Beck Depression Inventory-2nd edition scores for the depression state, Beck anxiety inventory scores for the anxiety state, and Montreal Cognitive Assessment scores for the cognition state before and the 10th day of treatment, 30th day of follow-up; study on mechanisms of rMS will be revealed through the resting motor threshold diversity of the motor cortex before and the 10th day of treatment, 30th day of follow-up. Baseline characteristics of patients will be summarized by groups and compared with Chi-squared for categorical variables, and analysis of variance or Kruskal–Wallis test for the continuous variables. Primary and secondary outcomes according to the measurement times are applicable to univariate repetitive measurement deviation analysis or analysis of variance, or Kruskal–Wallis test.

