### Secondary outcomes

2.10

Pittsburgh sleep quality index^[26]^ scores for the sleep quality of CI patients, Beck Depression Inventory-2nd edition scores for the depression state, Beck anxiety inventory scores for the anxiety state, and Montreal Cognitive Assessment scores for the cognition state before and the 10th day of treatment. Patients’ diary for tracking their mood, sleep, diet, adverse events, and others during the research. All the dropouts and causes will be documented in case report form.

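### The adverse-event comparison counts the waiting list's own r-DLPFC course (days 11 to 20) as events of an untreated arm

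*Protocol article*

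**What the plan says.** All references are to the protocol article.

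- **Exposure.** Section 2.7.3 leaves the waiting list untreated for 10 days, after which it is "treated same as the positive control group from the 11th day". Section 2.7.2.1 defines that course: "Participants will be treated 2 sessions per day for 10 consecutive days". It therefore occupies days 11 to 20.
- **Collection.** Section 2.8 says that "all adverse events are to be recorded and measured during treatment and the follow-up period". Section 2.1 sets 10 days of treatment followed by 20 days of follow-up, so collection covers days 1 to 30. Section 2.10 agrees, with a patient "diary for tracking their mood, sleep, diet, adverse events, and others during the research".
- **Analysis.** Under section 2.13.3, AEs from the "diary will be analyzed as a multiply variable", and "The number and percentage of patients with AE will be calculated and compared using Chi-squared test". It gives no time window, no cut-off when the waiting list starts stimulation, and no rule assigning events to the treatment received.
- **Label.** Section 2.12 calls the arm the "waiting-list control group (no treatment) randomly" assigned. The abstract summarises the schedule as "All will be given rMS at HT7 or rTMS at r-DLPFC or no treatment for 10 days, and then received 20-day follow-up" and does not mention the later course.

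**The concern.** Giving the waiting list active treatment after a delay is a legitimate choice, and section 2.7.3 states it openly. The difficulty lies in the safety comparison built on it.

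The waiting list is the trial's only source of an untreated event rate, and it supplies one only on days 1 to 10. Once days 11 to 30 are included, three things follow:

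- r-DLPFC against waiting list contrasts two arms that are each planned to receive one full r-DLPFC course. A real excess of events from r-DLPFC largely disappears.
- HT7 against waiting list becomes in effect HT7 against r-DLPFC. If HT7 carries less risk than r-DLPFC, HT7 could appear safer than no treatment at all.
- A single three-group test has the same weakness. Any systematic difference it picks up is HT7 differing from two arms exposed to r-DLPFC.

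This bears on the trial's rationale: the Discussion cites scalp, hearing and seizure risks of rTMS as reasons to look for an alternative. In addition, half of the participants planned to receive r-DLPFC (15 of 30 at 15 per arm, or 18 of 36 if the 54 in section 2.1 are enrolled) would be tabulated outside the r-DLPFC arm.

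**Working it through.** **Timeline.** AE collection covers days 1 to 30 and the waiting-list course covers days 11 to 20, so all 10 course days lie inside the collection period. This step needs no assumed rates.

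**Size.** The protocol has no AE rate or safety power figure to reproduce, so the following is an illustration. Assumptions:

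- risk of an AE per 10-day block: *u* = 2% to 10% without stimulation, *s* = 20% to 40% under r-DLPFC, *h* = *s*/2 under HT7;
- independent blocks, and post-stimulation risk back to *u*;
- every participant receives the planned course.

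Probability of at least one AE over days 1 to 30:

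- r-DLPFC arm: 1 − (1 − *s*)(1 − *u*)²
- waiting list: 1 − (1 − *u*)(1 − *s*)(1 − *u*), the same value
- 30 untreated days: 1 − (1 − *u*)³
- inflation of the waiting list: (*s* − *u*)(1 − *u*)²
- HT7 minus waiting list: (*h* − *s*)(1 − *u*)²

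Example, *u* = 0.02 and *s* = 0.40: the waiting list shows 1 − 0.60 × 0.9604 = 0.424, against 1 − 0.98³ = 0.059 for 30 untreated days. Inflation is 0.38 × 0.9604 = 0.365. HT7 minus waiting list is −0.20 × 0.9604 = −0.192.

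| *u* | *s* | Waiting list as planned | 30 untreated days | Inflation | HT7 minus waiting list |
|---|---|---|---|---|---|
| 0.02 | 0.20 | 0.232 | 0.059 | 0.173 | −0.096 |
| 0.02 | 0.40 | 0.424 | 0.059 | 0.365 | −0.192 |
| 0.10 | 0.20 | 0.352 | 0.271 | 0.081 | −0.081 |
| 0.10 | 0.40 | 0.514 | 0.271 | 0.243 | −0.162 |

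**Contrasts on days 1 to 10.** r-DLPFC minus waiting list is *s* − *u*, or +0.10 to +0.38. HT7 minus waiting list is *h* − *u*, or 0 to +0.18. Against 30 genuinely untreated days, HT7 would show (*h* − *u*)(1 − *u*)², or 0 to +0.173. The whole-study comparison turns this into −0.081 to −0.192.

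**Sensitivity.** If post-stimulation risk stays at 2*u*, r-DLPFC minus waiting list over the whole study is (1 − *s*)(1 − 2*u*)*u*. That runs from 0.60 × 0.96 × 0.02 = 0.012 to 0.80 × 0.80 × 0.10 = 0.064, still well short of the day 1 to 10 contrast. If *h* = *s*, the whole-study HT7 contrast is 0; it is negative only when *h* < *s*.

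**Rejection probabilities.** Exact enumeration of the uncorrected Pearson Chi-squared test at 5%, over *u* in {0.02, 0.05, 0.10} and *s* in {0.20, 0.30, 0.40}:

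| Test | Per arm | Days 1 to 10 | Whole study |
|---|---|---|---|
| r-DLPFC vs waiting list | 15 | 0.101 to 0.820 | 0.046 to 0.055 |
| r-DLPFC vs waiting list | 18 | 0.123 to 0.895 | 0.047 to 0.065 |
| Three groups (2 df) | 15 | 0.092 to 0.644 | 0.074 to 0.184 |
| Three groups (2 df) | 18 | 0.114 to 0.768 | 0.081 to 0.222 |

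Over the whole study, the two-arm test rejects at about its nominal level however harmful r-DLPFC is.

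**The case against.** The strongest reply is that this is mostly silence. Section 2.13.3 does not say that AEs are compared over days 1 to 30 or that the waiting list is included, and windows and relatedness rules are often left to a full protocol or SAP that is not shown. An unseen plan could indeed add a window. But the article does fix a collection period, a start of r-DLPFC inside it, and a comparison of patients with AEs from that same diary. Those statements together produce the problem. Section 2.13.3 names no groups, but section 2.13.2 uses the Chi-squared test on diary variables between groups, so that is the natural reading.

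Section 2.8 also links headache, scalp discomfort and tinnitus to rTMS, and skin numbness to HT7 stimulation. A scalp event in the waiting list after day 11 would therefore be recognisable. That is fair, but the text is descriptive, and section 2.13.3 counts any patient with an AE.

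Other points stand as limits:

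- The abstract ties the absence of treatment to 10 days and section 2.7.3 is open about the later course, so nothing is concealed.
- Withdrawals (section 2.3.3) and the eszopiclone drop-out rule (section 2.8) mean actual exposure need not be equal between arms.
- This is a small pilot, and the HT7 against r-DLPFC comparison is not touched.
- Counts on days 1 to 10 will be sparse. In the two-arm test the expected number with an AE per arm is 15 × (*s* + *u*)/2, or 1.65 to 3.75 (at most 4.5 with 18 per arm), so the Chi-squared approximation is weak.

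**Conclusion.** The concern holds. As written, the plan counts r-DLPFC events from days 11 to 20 in the arm labelled untreated, and every AE comparison that includes the waiting list is affected. The equality of planned exposure between the r-DLPFC arm and the waiting list rests on the text alone. The sizes rest on assumed rates: inflation of 8.1 to 36.5 points, an r-DLPFC excess reduced to 0 (1 to 6 points if post-stimulation risk is doubled), and an HT7 contrast of −8 to −19 points that needs HT7 to carry less risk than r-DLPFC. Pilot status and sparse counts limit the importance of the point but not its validity. It should be corrected, with medium confidence because a fuller plan might already contain a window.

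**What to change.** In section 2.13.3, state that any between-group AE comparison involving the waiting list, including a three-group test, uses days 1 to 10 only. Keep HT7 against r-DLPFC over the full period.

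Add a descriptive AE table by treatment received: HT7, and r-DLPFC pooled from the positive control and from the waiting list from day 11. Use equal windows from first stimulation, for example 20 days (days 1 to 20 for the arms treated at once, days 11 to 30 for the waiting list). This brings the waiting list's r-DLPFC experience into the r-DLPFC safety summary.

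The cost is one or two sentences and one table. No new data are needed, because the diary runs through follow-up and the record cards in section 2.14 hold treatment dates. The downside is that events after day 10 leave the randomised contrasts with the waiting list and appear only in HT7 against r-DLPFC and in the exposure table.

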### Adverse events observation

2.8

It could be that patients with epilepsy or headache, scalp discomfort, and tinnitus at stimulating are more likely related to rTMS. Regional skin numbness around the HT7 acupoint occur in patients is probably connected to rMS at HT7 acupoint. With the patients’ diary, all adverse events are to be recorded and measured during treatment and the follow-up period. Serious adverse events should be reported to the principal investigator immediately. All details will be documented, coil location and stimulus intensity adjustment (avoid the more sensitive orbitofrontal cortex, 100% RMT → 80% RMT), as well as appropriate medical care will be given at once. For the participants with severe CI during study, they would be administered with Eszopiclone tablets (3 mg Qn). However, if the subjects cannot tolerate the 80% RMT intensity and/or take Eszopiclone tablets more than twice a week, they will be considered as drop outs.

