### Interventions

2.7

Interventions are selected base on the theory of TCM and expertise. The physicians involved have received their practitioners’ license from China's National Health and Family Planning Commission as well as acupuncture and rTMS clinical skill training, who have worked for more than 3 years. Subjects in experimental group will receive rMS at HT7, and others in control group will receive rTMS at r-DLPFC or waiting treatment. Besides, if the symptoms were severe or do not improve during the treatment or the waiting period, Eszopiclone tablets (3 mg Qn) would be allowed.

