##### rMS at HT7 acupoint

2.7.1.1

The rTMS therapeutic apparatus (CCY-II model; Wuhan YiRuiDe Medical Supplies New Technology Co Ltd, Wuhan, China) were used. rTMS is applied to treat CI according to the modern neuro-rehabilitation theory. Acupoint is only left HT7 (*shenmen*) acupoint according to the TCM theory. After preparation, test the resting motor threshold (RMT): the participants will take the sitting position, keep the mood stable and the muscles relaxed. During stimulating M1 region, the coil will be tangent to the scalp, and it will be advisable to adjust the coil to get the maximum amplitude and the best repeatability of motor evoked potential. The stimulus intensity will begin from 30% and gradually increase at a rate of 2.5%. The minimum stimulus intensity (RMT) will be the abdominal contraction in the abductor pollicis brevis muscles of contralateral thumb in 5 out of 10-times consecutive stimuli; locate the stimulus area: the stimulation coil will be placed at the left HT7 acupoint (on the anteromedical aspect of the wrist, radial to the flexor carpi ulnaris tendon, on the palmar wrist crease) (Fig. 2); set the stimulus parameters: the standard mode is selected as the stimulus mode, for instance the frequency as 1 Hz, the total pulses number as 1800, and the intensity as 25% RMT.^[24]^ Start the stimulation after checking the above parameters, and then remove the coil flap after the stimulation. Participants will be treated 2 sessions per day for 10 consecutive days.

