### Statistical analysis

2.13

Data analysis will be based on intention-to-treat analysis and/or per-protocol analysis principle in the light of data missingness. We will also evaluate the group effect by comparing the analysis results between the above 2 data sets to evaluate robustness of our analytical results.

All data will be analyzed using SPSS23.0 (v23.0; SPSS Inc, Chicago, IL) by 3rd-party statistician. A *P* value <.05 will be considered as significant. Descriptive statistics will be performed with mean, standard deviation, maximum, minimum, and so on by groups and time.

Baseline characteristics of patients will be summarized by groups and compared with Chi-squared for categorical variables, and analysis of variance (ANOVA) (normal distributions) or Kruskal–Wallis test (non-normal distributions) for the continuous variables. Primary and secondary outcomes according to the measurement times are applicable to univariate repetitive measurement deviation analysis or ANOVA or Kruskal–Wallis test. If there is a violation of distribution assumption, appropriate transformation will be used.

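### Nightly rescue eszopiclone is permitted, yet more than two uses a week makes a patient a dropout; with an intolerance rule that HT7 stimulation cannot trigger, exclusion may come to depend on outcome and on arm

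*Protocol article*

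**What the plan says.** **Rescue is permitted nightly.** Interventions (2.7) states: "if the symptoms were severe or do not improve during the treatment or the waiting period, Eszopiclone tablets (3 mg Qn) would be allowed". Adverse events observation (2.8) repeats the same regimen: "For the participants with severe CI during study, they would be administered with Eszopiclone tablets (3 mg Qn").

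**Rescue use leads to dropout.** The next sentence of 2.8 sets a limit for those who "take Eszopiclone tablets more than twice a week, they will be considered as drop outs".

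**Intolerance leads to dropout.** That sentence applies the same label "if the subjects cannot tolerate the 80% RMT intensity". It follows an intensity step described as "avoid the more sensitive orbitofrontal cortex, 100% RMT → 80% RMT". The r-DLPFC arm is stimulated at 100% RMT (2.7.2.1). For HT7 the protocol sets "the intensity as 25% RMT" (2.7.1.1). The waiting list is untreated for 10 days and then receives the comparator treatment from day 11 (2.7.3).

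**Analysis.** Statistical analysis (2.13) begins "Data analysis will be based on intention-to-treat analysis", but the sentence goes on to and/or per-protocol, in the light of missing data. Results from the two sets are to be compared for robustness. The Withdrawal criteria (2.3.3) name neither the rescue limit nor the 80% RMT rule. They do withdraw anyone with fewer than 20 sessions or without 10 consecutive treatment days.

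**The concern.** Two statements about rescue cannot both be applied as written: following the permission breaches the limit. The trigger for rescue is severe or unimproved insomnia, which is what the ISI, a primary outcome, measures. A dropout rule keyed to rescue is therefore keyed to a poor value of the primary outcome.

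The intolerance rule has a different problem. It is tied to a stimulation intensity that one of the two active arms never receives, so it cannot act equally on the two sides of the HT7 versus r-DLPFC comparison, which is the noninferiority comparison.

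What is at stake is who contributes to the day-10 and day-30 comparisons. If patients labelled dropouts are not assessed or not analysed, the remaining groups are selected on outcome and, for intolerance, on arm. With 15 patients per arm, the loss of two or three is not negligible.

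**Working it through.** **1. Rescue permission against the rescue limit.** Qn is every night: 7 doses a week, or 10 over the 10-day treatment period. The limit is 2 a week, or 10 × 2/7 ≈ 2.9 over 10 days. A patient taking the permitted nightly dose passes the limit at the third dose, within the first week. The conflict lies between 2.7 and 2.8 and also inside 2.8.

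**2. Which arms the 80% RMT rule can reach.**

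| Arm | Intensity | Can a patient fail to tolerate 80% RMT? |
|---|---|---|
| HT7 | 25% RMT at the wrist | No, 80% is never given |
| r-DLPFC | 100% RMT, step to 80% | Yes |
| Waiting list, days 1–10 | None | No |
| Waiting list, from day 11 | As r-DLPFC | Yes |

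This follows from the text without any assumption.

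**3. Which arms the rescue limit can reach.** The wording is the same for all three. It removes patients unequally only if sleep differs between arms. That is to be expected for an untreated group, but it is an expectation and not something the protocol states.

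**4. What happens to dropouts in the analysis.** They leave any per-protocol set. For intention-to-treat the text does not settle it: the choice of set is linked to missing data, which these rules may themselves create, and nothing in the article says that dropouts are still assessed at day 10 and day 30.

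**5. Illustration of size.** The documents give no ISI standard deviation, mean or rescue rate, so every input here is assumed: day-10 ISI normal with SD 5; active mean 14; waiting-list mean higher by D = 3, 4 or 5; 70% of patients with ISI above a cut-off c exceed the rescue limit and are excluded; c = 20 or 22.

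With z = (c − mean)/5 and p = 1 − Φ(z):
- proportion excluded = 0.7p
- fall in the arm's mean = 0.7 × 5 × φ(z)/(1 − 0.7p)
- observed difference = D − (fall in waiting list) + (fall in active arm)

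Active arm, c = 20: z = 1.2, p = 0.115, φ = 0.194, so 8.1% excluded and a fall of 3.5 × 0.194/0.919 = 0.74. With c = 22: 3.8% excluded and a fall of 0.40.

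| D | c | Waiting list excluded | Fall in waiting list | Observed difference | Loss |
|---|---|---|---|---|---|
| 3 | 20 | 19.2% | 1.44 | 2.30 | 23.5% |
| 3 | 22 | 11.1% | 0.95 | 2.45 | 18.3% |
| 4 | 20 | 24.1% | 1.70 | 3.04 | 24.0% |
| 4 | 22 | 14.8% | 1.19 | 3.21 | 19.7% |
| 5 | 20 | 29.5% | 1.94 | 3.80 | 24.0% |
| 5 | 22 | 19.2% | 1.44 | 3.96 | 20.8% |

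Exclusion is thus about 4–8% in an active arm and 11–29% on the waiting list, and the difference shrinks by 18–24%.

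**6. Between any two arms.** Suppose instead that everyone above one common severity cut-off is excluded, with the cut-off removing 10% or 20% of the better arm. By simulation, a true difference of 0.5 SD then appears as 0.32 or 0.26 SD. With no true difference, exclusion is equal and there is no bias. If HT7 were truly worse than r-DLPFC, such shrinkage would favour a noninferiority conclusion. No figure can be put on the 80% RMT rule, because the documents give no intolerance rate.

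**The case against.** The strongest reply is that a dropout label is not removal from the analysis. The article never says that outcome collection stops, or that these patients leave the intention-to-treat set, and such handling is commonly left to a full protocol or analysis plan. This stands: exclusion is certain only for a per-protocol set. What remains is that the and/or wording, governed by missing data, gives no assurance that they are kept.

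Four stronger readings are tempting, and the documents do not support them.
- *The rescue rule removes patients selectively by arm.* It is worded alike for all arms. Only the 80% RMT rule is arm-specific on its face.
- *Only comparator patients can be lost through intolerance.* Waiting-list patients receive r-DLPFC stimulation from day 11, and an HT7 patient who stops early, for example because of wrist numbness, is withdrawn under 2.3.3.
- *The comparator's tolerability cost is hidden.* Secondary outcomes (2.10) and Quality control (2.14) record dropouts and their reasons, and Safety evaluation (2.13.3) compares adverse events. The ISI comparison among retained patients would still not reflect that cost.
- *The plan contradicts an intention-to-treat commitment.* The full sentence in 2.13 includes per-protocol as an alternative, so there is no unconditional commitment to contradict.

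One could also read Qn as at night when needed, up to twice a week. That would ease the conflict, but neither section says so. Finally, this is a declared pilot with acknowledged limits, which lowers the severity but does not resolve the inconsistency.

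**Conclusion.** The point holds in a limited form. Two things are firm from the text: the rescue permission (7 doses a week) and the rescue limit (2 a week) conflict, so permitted use, prompted by a poor outcome, makes a patient a dropout; and the 80% RMT rule cannot be met under HT7 stimulation.

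The bias is conditional. It arises if dropouts are not assessed or are left out of the primary comparison, which 2.13 leaves open. Exclusion would then depend on the primary outcome and, for intolerance, on the arm. The rescue limit would tend to shrink differences if the arms differ in sleep. The 18–24% shrinkage rests wholly on assumed inputs, covers only active versus waiting list, and takes the difference without rescue as the truth. It is not the gain from the fix, because keeping rescued patients brings in the effect of the rescue drug, which may also narrow the difference. This should be fixed, but it does not by itself invalidate the trial.

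**What to change.** 1. The sponsor should reconcile Withdrawal criteria (2.3.3), Interventions (2.7) and Adverse events observation (2.8) on rescue use and dropout, and state which arms the 80% RMT rule covers. Which clinical rule is right is for the sponsor and is not judged here.
2. Separate dropout status from outcome assessment: collect day-10 and day-30 ISI and RMT from these patients at the scheduled visits.
3. Replace the and/or in 2.13 with an as-randomised (intention-to-treat) primary analysis, and confine exclusion for rescue use or intolerance to the per-protocol sensitivity analysis.
4. Report rescue nights (from the patient diary) and intolerance by arm.

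The cost is protocol wording and continued assessment at visits already planned. The small downside is that outcomes after rescue reflect treatment plus rescue, which must be stated when results are interpreted.
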